#### 4.6. Inclusion Criteria for the non-interventional study (Part IV)

1. Up to 20 participants must have a molecular genetic diagnosis of FRDA, consisting of a GAA-repeat expansion on both alleles of the FXN gene.
2. Up to 20 HV participants
3. Participants are over the age of 18 years, living in the UK and registered with a GP.
4. Participants must provide informed consent. If written consent is not possible due to physical incapacity, written consent on behalf of the participant will be sought from the participant's relatives or carer.
5. Women of child-bearing potential must have a negative urine pregnancy test.

#### 4.7. Exclusion Criteria for the non-interventional study (Part IV)

1. Contraindications to MRI including, but not limited to: intracranial aneurism clips (except Sugita), history of metal lathe work or possibility of intra-orbital metal fragments, pacemakers and non-MR compatible heart valves or other non-MR compatible implants, history of claustrophobia or participant feels unable to lie still on their back for a period of 60-90mins in the fMRI scanner.

#### 4.8. Participant Completion

Participants will be considered complete for the purpose of the interventional study once they have completed all procedures at the end of interventional study visit. The end of interventional study is defined as the last visit of the last participant (LVLP) undergoing the interventional trial.

FRDA participants who will take part in part IV of the study will have their last visit at 9-12 months.

We do not recommend that participants continue to take nicotinamide post-study as further clinical trials are required to determine whether or not nicotinamide is safe and is of clinical benefit to FRDA patients. If

participants still decide to take nicotinamide against our advice, they will be referred to their GP with recommendation of regular safety follow up to evaluate any nicotinamide-induced toxicity. We may request the FRDA participants consent to come in for visits at the Imperial CRF at the CI's discretion. Blood tests (FXN/chromatin, safety bloods etc) and neurological and medical examinations (SARA, SCAFI, ADL, ECG, vital signs etc) may be performed at these visits.

All FRDA participants will be offered the possibility to enter a large scale follow-on study which is being planned to define efficacy based on acceptable endpoints for this condition.

#### **4.9. Withdrawal of Participants from Study**

At any time, participants may withdraw from the study (i.e. withdraw consent to participate) at their own request and without giving reasons. Participation in the study may be discontinued at any time at the discretion of the CI and in accordance with their clinical judgment. No disadvantage will arise for any participant who withdraws consent for participation at any time or who is withdrawn from the study by the CI.

Reasons for discontinuation of study treatment will be recorded on the electronic Case Report Form (eCRF) in any case and may include the following:

- Participant's request for withdrawal
- CI's decision that discontinuation is in the best interest of the participant
- Non-compliance with the regimen and timing
- Development of an intolerable AE due to study participation as determined by the CI, participant or both
- Development of an intercurrent illness, condition, or procedural complication, which would interfere with the participant's continued participation
- Discovery that the participant entered the study in violation of the protocol or occurrence of a significant protocol violation during the study
- Data that becomes available that raises concern about the safety of the study drug so that continuation would pose potential risks to the participant
- Participant becomes pregnant
- Participant is lost to follow-up
- Any participant who discontinues treatment for medical reasons, e.g. because of AEs or clinical laboratory abnormalities, should be followed up at medically appropriate intervals in order to evaluate the course of the event and to ensure reversibility or stabilisation of the abnormality or event. The subsequent outcomes of these events will be recorded on the eCRF. However, if these events are attributable to deterioration of the disease, no such measures will be suggested.
- If a participant fails to return for a scheduled visit, a documented effort must be made to determine the reason. All attempted contact (telephone, emails or letters) must be filed in the participant's medical notes.

An Interventional End of Study (EOS) Visit will be done for each participant who completes the interventional study or who receives any study drug and withdraws prematurely from the study.

It may be possible in certain exceptional circumstances for a participant to withdraw from one part and enter another part of the study (for example: withdraw from Part II however enter Part III) however this arrangement would be agreed by the CI and participant.

In case of premature termination or suspension of the study, the CI will promptly inform the Research Ethics Committee (REC) and Medicines HealthCare Regulatory Agency (MHRA) of the termination or suspension and the reason for that action.

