**Comparator therapy, dose and mode of administration:**

No comparator therapy will be used in this study (pre-post therapy study design).

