### **Long term assessment of FRDA participants taking nicotinamide daily over a two month period, Part III**

If the multiple dose dosing regimen of nicotinamide in Part II is well tolerated and changes in FXN level are observed, all participants (including those who were scheduled to receive no drug in part II) will be offered to enter Part III. Participants who took part in part I but not in part II of the study may also participate. These participants may require re-screening. This decision will be taken by the CI. If required, additional participants will undergo screening and if eligible may enter directly into this part of the study. Participants who took part in Part II will be given the weekly drug supply and diary on Part II Day 5. Participants who took part in Part I but not Part II or participants who will directly enter Part III will be given the weekly drug supply and diary at their screening visit (only once determined eligible) or by courier / recorded delivery post. Their next visit will be Part III, week 1.

Participants who were 'on drug' in Part II will take their MTD already established over the course of two months. If any AEs occur that in the CI's opinion may put the safety of the participant at risk, the dose schedule will be adjusted. If a participant was on 'no drug' in Part II or due to enter Part III directly they will start at a low dose of nicotinamide (typically 2g) which will be gradually escalated in the absence of any AEs which in the CI's opinion may put the participant's safety at risk.

If the participant stops taking nicotinamide for several days (for safety reasons), only once the participants AEs are fully resolved, the CI may decide to add this drug interruption period onto the end of the two month period.

To ensure that sustained FXN upregulation is achieved, the nicotinamide PK/ pharmacodynamic (PD) relationship (i.e. time to nicotinamide steady state vs. upregulation of FXN) will be evaluated at each weekly visit and the daily dose regimen may be modified from once to twice a day [i.e. from 6 grams (or MTD) Once Daily (OD) to 3 grams (or ½ MTD) twice a day (BD)]. In some instances, manufacturing restrictions (i.e. nicotinamide tablets of 500mg) render the division of the dose into two equal doses, for BD dosing, impossible. In these cases patients will receive a slightly different dose in the morning to the evening.

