## **8.6. Assigning Causality of the Adverse Event to the IMP**

The CI or delegates will determine the relationship of each AE to study drug (i.e., causality) by using the classification criteria: 'related', 'probably related', 'possibly related' 'unlikely to be related' or 'not related'. If an AE is classified as either 'possibly related' or 'probably related', it should be considered to be an ADR. Descriptions of the six classification categories are as follows:

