### **8.6.1. Not Related**

Exposure to the IMP has not occurred; administration of IMP and the AE are not reasonably related in time; or the AE is considered by the CI or delegates to be due to a pre-existing condition, a known manifestation of the target disease, a recurrent condition, or is likely explained by environmental or diagnostic therapeutic factors or was pre-existing and did not deteriorate.

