### **8.6.2. Possibly Related**

The AE occurred during or within a reasonable period of time after administration of the IMP, or a pre-existing event worsened within an appropriate period of time after administration of the IMP, but the AE could be explained equally well by factors or causes other than exposure to the IMP.

This category will also be used if there is a lack of information, or insufficient or conflicting evidence exists for classifying the causality of the AE.

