### **8.6.3. Probably Related**

The AE occurred during or within a reasonable period of time after administration of the IMP or a pre-existing event worsened within an appropriate period of time after administration of the IMP, and at least one of the following criteria is applicable:

- the event could not be explained by the clinical condition or history of the participant, environmental or toxic factors, or other diagnostic or therapeutic measures;
- the event was an expected ADR associated with study treatment or a class-labeled drug effect;
- the AE subsided or disappeared after withdrawal or dose reduction of study treatment; or
- the AE recurred after re-exposure to study treatment.

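### Section 4.9 waives clinician follow-up for non-serious events that stop nicotinamide and are attributed to Friedreich's ataxia, which modestly weakens the check on that attribution

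*Protocol*

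**What the plan says.** Section 4.9 (Withdrawal of Participants from Study) sets a general rule. A participant who stops treatment for medical reasons, such as an adverse event or an abnormal laboratory value, "should be followed up at medically appropriate intervals in order to evaluate the course of the event" and to confirm that it reverses or settles. The later outcome goes on the eCRF. The next sentence makes an exception: "However, if these events are attributable to deterioration of the disease, no such measures will be suggested".

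Three parts of section 8.6 bear on the exception:

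- Section 8.6 leaves causality to the chief investigator (CI) or delegates. An event rated *possibly* or *probably related* is treated as a drug reaction: "it should be considered to be an ADR".
- Section 8.6.1 allows *not related* when the event is "considered by the CI or delegates to be due to a pre-existing condition, a known manifestation of the target disease".
- Section 8.6.3 lists, among the criteria for *probably related*, that "the AE subsided or disappeared after withdrawal or dose reduction of study treatment".

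The Synopsis describes a pre-post design without comparator therapy. In Part III, "all participants (including those who were scheduled to receive no drug in part II) will be offered to enter Part III".

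**The concern.** When a participant stops the drug, the course of the event afterwards is direct evidence on whether drug or disease caused it. The protocol accepts this, because it makes improvement off drug a causality criterion. Section 4.9 nevertheless ends the planned clinical follow-up once the event is put down to the disease, and that is when the evidence starts to appear. A mistaken attribution to disease is therefore less likely to be found and corrected.

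This matters here for three reasons. Section 8 calls the study the first use of nicotinamide in Friedreich's ataxia. Section 3.2 makes safety and tolerability an objective. Part III, the two-month exposure, has no untreated participants against whom worsening could be judged. Drug effect and disease can also look alike: section 2.1 associates the disease with blindness, diabetes and cardiomyopathy, while the side-effect table in section 8.1 includes difficulty focusing the eyes and fatigue.

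**Working it through.** The plan gives no figure on this point and none needs recomputing. The check is a reading of the relevant sections against each other.

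1. **Which events lose follow-up?** Section 4.9 covers medical discontinuations in general. Sections 8.7.2 and 8.7.3 separately require serious events to be followed until they resolve or stabilise, whatever their cause. The exception therefore bites only on non-serious events that stop treatment and are attributed to disease.

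2. **Who decides, and knowing what?** The CI or delegates decide (section 8.6). There is no masked comparator, and allocation to no drug in Part II is at the CI's discretion and discussed with the participant (sections 4.1 and 7.10). The judgment is made with treatment known.

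3. **What follows from the judgment?** Attribution to disease has two effects. Under section 8.6.1 it suffices for *not related*, which keeps the event outside the drug-reaction rule in section 8.6. Under section 4.9 it also removes the interval follow-up. Yet under section 8.6.3 the off-drug course could have moved the event to *probably related*.

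4. **What does the waiver cover?** The words referring back to the measures can mean the follow-up alone, or the follow-up and the eCRF outcome entry in the sentence just before. The text does not settle which.

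5. **What observation remains?**
   - Section 8.2 still counts deterioration from the primary illness as an adverse event. Section 8.7.1 requires events to be recorded to the end of follow-up, with onset and duration.
   - Sections 4.1 (Part III), 7.7 and 7.10 have Part III participants keep a diary, which records adverse events, up to the end-of-study visit; section 4.1 has it completed each day.
   - Section 4.9 requires an end-of-study visit for anyone who received drug and withdraws early, without exception by cause. Section 7.11 places it 1 to 8 weeks into washout, with adverse event review, examination, FARS, SARA, SCAFI, speech assessment, ECG and laboratory tests.
   - A participant who is off drug but still in Part III would have the weekly visits in section 7.10.

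6. **What is lost?** For a non-serious, disease-attributed event followed by withdrawal, clinician contacts between stopping and the end-of-study visit are no longer planned. There is no duty to follow the event to resolution or stabilisation, and the outcome entry may be waived. Other medical discontinuations keep all of these.

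7. **Scale.** With 10 to 20 participants per part (Synopsis), one such event is 1/20 = 5% to 1/10 = 10% of Part III. The documents give no rate for such stops, and there may be none.

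**The case against.** The strongest defence is that the causal question is mostly answered anyway. The end-of-study visit is required whatever the attribution, and it repeats the ataxia scales and safety tests off drug. Section 8.6.3 asks whether the event eased, not when. This stands, and it is the main reason the point is minor.

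Section 8.6.2 also protects doubtful cases. Events explained equally well by another cause go to *possibly related*, and "This category will also be used if there is a lack of information". That helps when the investigator is unsure. It does not help when the investigator is confident of a disease cause and wrong.

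The clause has a sensible motive: true progression may never reverse or settle, so open-ended follow-up could be unachievable. It also withdraws a recommendation and does not forbid follow-up. Both are fair, but the first supports a stopping point and not a waiver.

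A reader might infer that these participants go unobserved after stopping, and might count the days from drug clearance to the end-of-study visit as a blind interval. The documents do not support this. The Part III diary is a planned daily record of adverse events up to that visit, although it is self-report and the protocol does not say separately how it runs after an early stop. Such a count would also assume that stopping drug means leaving the study. Section 4.9 speaks of discontinuing treatment and, separately, of withdrawing from the study, and Part III provides for safety interruptions of the drug.

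**Conclusion.** The point holds as a minor design weakness. For non-serious events that stop nicotinamide, a single unblinded attribution to disease both supports *not related* and removes the clinician follow-up that could revise that rating. The loss is clinician-observed course between stopping and the end-of-study visit and, on one reading, the eCRF outcome. It is not a loss of all observation.

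No effect is claimed on the primary frataxin endpoint, on handling of serious events or on the escalation rules. The conclusion assumes that at least one such stop occurs and that the participant leaves the visit schedule. A participant who stays in Part III off drug loses less, because the weekly visits continue.

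**What to change.** Delete the exception sentence from section 4.9. In its place, state that every medical discontinuation is followed at clinically suitable intervals until the event reverses or settles or, where worsening is progressive, up to the end-of-study visit. For such progressive worsening, record the outcome on the eCRF at that visit and have the CI or delegate reconfirm causality using the off-drug course. This also removes the doubt about whether outcome recording is waived.

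The cost is one deleted sentence, one added stopping rule, and a few extra contacts and eCRF entries for participants already due an end-of-study visit. The stopping point meets the concern about disease that never stabilises.

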#### 4.10. Prior and Concomitant Therapy

Participants may enter this study receiving any concomitant therapy except for those specifically prohibited in the exclusion criteria. The dose of concomitant treatments should remain stable for 8 weeks prior to entry in the study. The CI or delegates may prescribe additional medications (see 6.7) during the study, provided the prescribed medication is not prohibited by the protocol. Any additional medication or adjustment to medication must be recorded in the eCRF.

#### 4.11. Dose Reduction Guidelines for Potential Side Effects

Based on experience to date with nicotinamide the most likely side effect that might interfere with participant compliance is nausea/vomiting. Use of a VAS (shown below) to monitor this subjective effect combined with the dose-escalation study will establish if particular participants are susceptible and then the dose escalation adjusted to prevent excessive nausea.

##### Visual Analogue Scale:

How do you rate your nausea on a scale of 1 to 10, 1 being the least severe to 10 being the most severe?

1            2            3            4            5            6            7            8            9            10

In addition if clinically appropriate, anti-nausea agents (for example: domperidone or metoclopramide etc.) will be given as required. In order to avoid nausea in Part II, participants will be administered anti-nausea treatment prophylactically prior to dosing if required. In Part III, participants will be provided with rescue medication to take prophylactically prior to dosing (for example: domperidone 20 mg oral or metoclopramide) and post-dose if required (for example: domperidone 20 mg oral up to four times daily or metoclopramide). Participants will be asked to keep an accurate record of the use of rescue medication in the weekly trial diary.

Although nausea is the most likely side effect in the recently published ENDIT study which administered high-dose nicotinamide (3g/day) on a long term basis this side effect was rarely reported (<0.5%). It was also rarely reported in a study of higher doses of nicotinamide (6-9g) given to normal volunteers taking nicotinamide in tablet form (Horsman et al., 1993).

## 5. TREATMENTS

### 5.1. Study Product, Dose, and Route of Administration

The study drug product is Nicotinamide. Nicotinamide is a commercially available as Vitamin B3. 0.5g tablets are readily available under the trade name Nicobion from Teofarma.

### 5.2. Metabolism

Nicotinamide is readily metabolised in the liver and its metabolites are rapidly excreted via the kidney.

### 5.3. Pharmacokinetics

Nicotinamide has high bioavailability and is readily absorbed via the Gastrointestinal (GI) tract, it passes the blood brain barrier and when given orally reaches peak plasma concentrations within 30 mins to 1 hour. It is rapidly cleared from the circulation and has a wide tissue distribution. Pharmacodynamic studies in humans reveal a half-life of between 5 and 7 hours.

#### 5.4. Rationale for Nicotinamide Dose Selection

The dose range chosen in this study is based upon those previously used in humans in long-term studies (ENDIT, Gale et al., 2004) and short-term studies (Horsman et al., 1993) as well as the levels required to achieve upregulation of FXN in cells obtained from FRDA participants and in a mouse model of FRDA (see above). Mouse studies suggest that a single dose can lead to upregulation of FXN 24hrs post-dose therefore daily dosing is likely to be sufficient. It is difficult to extrapolate directly from the mouse to the human due to species differences. However, the mouse studies are useful in that they showed upregulation of FXN in the affected tissues. At present it is not known what dose would be effective in humans which is the purpose of this study.

The dose range chosen here was based on 2 criteria: 1) doses shown to be well tolerated in previous studies in humans (Horsman et al., 1993; Gale et al., 2004) and 2) our studies on primary lymphocytes which showed that exposure to nicotinamide between 1-10mM will upregulate FXN by up to 3 fold *in vitro* (see background). Oral dosing of nicotinamide at 6g has previously been shown to achieve plasma nicotinamide concentrations within this range in human volunteers (Stratford et al., 1996). FXN levels in asymptomatic carriers are 40-50% of normal (Pianese et al., 2004) and FRDA patients develop the disease at levels less than 30%. Therefore, a 1.5 to 5 fold upregulation would potentially restore FXN levels to those found in asymptomatic individuals. However, even more modest upregulation may be of therapeutic benefit. Therefore, for this study which will also look at tolerability we decided on a dose range between 2g and 8g daily. If effective in upregulating FXN towards carrier levels and/or well tolerated further studies will be designed to assess nicotinamide efficacy in FRDA patients.

#### 5.5. Study Product

A highly purified form of nicotinamide which has been shown to be well tolerated orally and is readily available for therapeutic use will be used for this study. The preparation of nicotinamide has been sourced by the Hammersmith Hospital Pharmacy who will dispense the drug. The IMP may be dispensed up to 2 days prior to the participant's visit. In Part I, the IMP will be dispensed at each visit. In part II, the IMP will be dispensed for the whole week. In Part III, the IMP will be dispensed at each weekly visit.

Participants will be given the drug supply required either on PIID5 (for participants participating in Part II) or at the screening visit / recorded delivery post (for participants who participated in part I but not in part II / participants who will directly enter into Part III) until their next visit (Part III, week 1).

